#### Eligibility Criteria

The inclusion and exclusion criteria stated below were refined during the feasibility trial [74] to maximise real world applicability to the individuals comprising the prisoner population who are identified to be at risk of suicide and seeking a psychological intervention. The inclusion criteria are (i) person sentence to imprisonment in a male prison, (ii) aged 18 years or over, (iii) at current risk of suicide behaviour as indicated by currently being on the host prison’s ACCT system, or on the ACCT system within the four weeks prior to consent, (iv) able to complete a brief battery of self-report measures with breaks if needed, and (v) willing to consent to being subject to a ‘holding order’ to require them to remain within the host prison for the duration of their participation in the trial. The exclusion criteria are (i) planned release within the next 9 months, (ii) insufficient knowledge of English to enable adequate participation in the assessment process, (iii) deemed by prison staff to be too dangerous/elevated risk of harm to the researcher, and (iv) considered by researcher to be lacking capacity to provide informed consent, according to the British Psychological Society’s code of human research ethics.

(http://www.bps.org.uk/sites/default/files/documents/code_of_human_research_ethics.pdf).

#### Participant Recruitment

Previous feasibility trials [74, 83] enabled the development of a recruitment strategy that proved acceptable and effective, which informed the strategy for the current trial. To launch the study at each site, all governor-grade staff will be invited to a brief meeting to talk about the study. Additionally, information about the study, including eligibility criteria, will be distributed to all prison staff via email, team briefings, and other existing dissemination channels deemed appropriate by the host prison governor. In addition to the launch events, the research team will seek to ensure continuing commitment to supporting the trial is maintained by the prison governors. Senior management support for this trial is crucial in it achieving success, and this shall remain a high priority issue for the research team throughout the trial. Regular communication between the prison governors and the Chief / Principal Investigators will be ensured through project briefings and attendance at Senior Management Team meetings at each host prison.

#### Participant identification and initial approach

Each host prison holds a list of prisoners who are, or who have recently been, cared for under the ACCT system [57]. The research team will work with the Safer Custody link person in each of the four prisons to identify potential participants who meet the eligibility criteria. Previous research has highlighted that successful recruitment in prisons tends to be associated with friendly, respectful, face to face approaches made at the cell door by enthusiastic researchers; it is generally unacceptable for prison staff to be used as gatekeepers as this could bias recruitment [51]. However, members of the research team should not have access to confidential information about potential participants prior to obtaining consent. To address this, the research team will be informed of potential participants who have expressed in interest in being approached. However, individual prisons operate differently and this can impact upon how potential participants are approached. Therefore, the research team will work flexibly with the individual prisons to develop an effective and safe protocol for approaching potential participants.

#### Consent and eligibility

After an expression of interest has been received, the researcher will make the initial approach. This approach will be made verbally and then, if interested, the Participant Information Sheet will be supplied as well as an opportunity for further discussion. Potential participants will be offered a minimum of 24 h to consider the information and whether they would like to take part in the study. Showing sensitivity to reduced literacy levels in this population, the researcher will informally gather information about participants’ reading ability from prison staff prior to making the approach. The researcher will offer to read the PIS aloud to the participant, or, when appropriate, the participant can read the PIS themselves. The researcher will check that the potential participant meets the eligibility criteria, including their willingness to be to be subject to a ‘holding order’ to remain in their host prison for the duration of their participation in the trial. After adequate time has been given, all queries have been addressed and the research team is confident that the potential participant understands the trial and all requirements, they will be consented into the trial.

Consent will be taken by a member of the trial team who has completed Good Clinical Practice (GCP) training, is suitably qualified and experienced, and who has been delegated by the PI to undertake this activity (and this delegation is clearly documented on the delegation log). Participants will provide written consent prior to any trial-related procedures being undertaken. If the researcher reads the PIS and consent form to the participant then another member of staff will witness that the full PIS and consent form have been read aloud to the participant. In these instances, there is a space on the consent form for the witness to also sign. The original, wet-ink signed copy of the participant information sheet and consent form(s) should be retained in the Investigator Site File. Copies of the completed form will be given to the participant and the prison GP.

If new safety information results in significant changes in the risk/benefit assessment, the participant information sheet and associated consent form would be reviewed and updated if necessary. If the participant information sheet and consent form are updated, all participants (including those already being treated), would be informed of the new information, given a copy of the revised documents and asked to re-consent to continue in the trial.

The study will involve vulnerable individuals since the sample will be drawn from the prisoner population and some of its participants may have ongoing mental health problems and/or suicidal ideation. The provision of participant informed consent and no sense of coercion is paramount, and the research team involved in this trial will be careful to explain all aspects of the study to participants in order to ensure that they understand what will be asked of them. If the researcher has any doubt over a participant's capacity to consent, the participant will be excluded from the study. Given the unique problems of gaining consent in a custodial setting, extra emphasis will be given to the potential participants' rights to consent/not to consent and also their right to withdraw at any time, without the need to give a reason for doing so, free of any coercion or negative consequences/ access to services or privileges. If participants do withdraw consent to continue in the study, any information already given by the participant will remain part of the research provided they agree. If participants withdraw consent to continue in the study and withdraw consent for their data to be used in the study, then their data will be removed from the final analysis.

#### Patient registration/randomisation procedure

Immediately following consent and completion of baseline assessments, eligible participants will be randomised to one of the two intervention arms (PROSPECT programme plus TAU or TAU alone). A web-based randomisation system will be designed, using the Clinical Trials Unit’s (CTU) bespoke randomisation system. The randomisation system will be created in collaboration with the trial analyst/s and the CI and maintained by the CTU for the duration of the project. It will be hosted on a dedicated server within the CTU. The CI or delegate will request usernames and passwords from the CTU. System access will be strictly restricted through user-specific passwords to the authorised research team members. It is a legal requirement that passwords to the randomisation system are not shared, and that only those authorised to access the system are allowed to do so. If new staff members join the study, a user-specific username and password must be requested via the research team from the CTU and a request for access to be revoked must be requested when staff members leave the project. Study site staff experiencing issues with system access or functionality should contact the CI or delegate (e.g. Trial Manager) in the first instance.

Participant initials and date of birth will be entered on the randomisation system, NHS number, email addressed, participant names and addresses and full postcodes will not be entered into the randomisation system. No data will be entered onto the randomisation system unless a participant has signed a consent form to participate in the trial. Randomisation will be undertaken by recruiting site staff, by authorised staff logging onto the online randomisation system. A full audit trail of data entry will be automatically date and time stamped, alongside information about the user making the entry within the system.

The research team will undertake appropriate reviews of the entered data, in consultation with the project analyst for the purpose of data cleaning. No data can be amended in the system, however the CI or delegate (e.g. Trial Manager) may request the CTU to add notes against individual subject entries to clarify data entry errors. Upon request, the CTU will provide a copy of the final exported dataset to the CI in.csv format and the research team will onward distribute as appropriate.

Randomisation will be at the level of the individual using the method of block randomisation with randomly varying block size stratified by prison site (NW1, NW2, YH1, YH2) and previous suicide attempt (No, Yes).

#### Methods to protect against sources of *bias*

The following measures will be put in place to protect against potential sources of bias. An independent third party will perform the randomisation of participants to the trial arms which protects against allocation bias. Randomisation will take place only when potential participants have consented to participate and baseline data has been collected and data entered onto the eCRF. Researchers performing the assessments will be blind as to the participant’s treatment allocation with precautionary strategies employed to prevent the researcher from becoming unblinded which will include (i) practitioners to consider room use and diary arrangements in light of potential breaks of masking; (ii) participant reminded by researcher not to talk about treatment allocation, and (iii) researcher to be prevented sight of participant’s full clinical notes until final assessments have been completed. In order to maintain the blind, therapy only assessments will be undertaken by the practitioners delivering the intervention and recorded on separate eCRF which will not be accessible or visible to the researchers. Blind breaches and potential blind breaches will be recorded and monitored and where possible another researcher will undertake follow-up assessments in replacement of a researcher that has become unblinded. All variables have been defined prior to the RCT taking place. Intention-to-treat analyses will be used. Participant throughput will be recorded, e.g., reasons potential participants opted not to participate. Reasons why participants dropped out of the trial will be recorded, if available. The CTU will set-up and manage electronic data capture for all RCT data required for analysis. The research team will undertake appropriate reviews of the entered data.

#### Sample size calculation

We use an approach based on a simple t-test for the between group comparison in the primary outcome which is specifically designed to account for differential clustering or partial nesting between the two arms. It is implemented in –clsampsi- in Stata. This approach requires the following assumptions:Effect size: We have powered our trial on the basis of clinical superiority compared to treatment as usual, and will conduct our analysis accordingly. We have powered to detect a standardised effect size of 0.36. This equates to an approximate mean difference of 3.9 in the primary outcome (Beck Scale for Suicide Ideation, BSSI) or 60% reduction in SB using estimates derived from our pilot RCT [74].Practitioner number: From our planned staffing of 4 practitioners at any one time, we have allowed for 7 practitioners to be used during the course of the whole trial (to account for practitioners leaving and being replaced). This also helps to improve the generalisability of the trial. We allow for a variance in the number of participants seen per practitioner (i.e. that this follows a Poisson distribution).Clustering: We account for differential clustering of 7 practitioners over trial duration in treatment plus TAU arm, average number of patients per practitioner of 18 and ICC = 0.01. No prior estimate of the ICC is available, but we consider this a conservative estimate to what is typically found in psychotherapy trials. We will include pre-specified prognostic variables for the outcome in our analysis models to further reduce the ICC. This approach is robust to observed increases in ICC as the number of practitioners (clusters) increases. For the calculation, we consider the control arm as clusters of size 1 with ICC = 0.Power: We assume a conservative baseline-endpoint correlation of 0.6 (0.6 in pilot, 95% CI 0.4–0.7), a two-sided significance level of 0.05 and statistical power of 90% with equal allocation to two arms. Given these assumptions, an analysis set of 250 (125 per group) has 80% power to detect an effect size of 0.36. Power will be increased by inclusion of baseline covariates where possible.Attrition: Although attrition rates for prison-based trials can be over 50% (e.g. [8, 70]), our pilot trial was sufficiently resourced to enable research staff to maintain regular contact with participants, resulting in an attrition rate of 30%.

To achieve a target sample size of *n* = 250, and accounting for expected attrition of up to 30% [74], a total of 360 participants will be recruited with recruitment split in proportion to the prison capacity of each of the host sites. According to our pilot RCT, we can also estimate 40% of people will decline to take part and a further 10% will be excluded for security reasons, therefore approximately 670 potential participants will be screened to determine eligibility (see Fig. 1).

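### The sample size section gives both 90% and 80% power for the same design; the listed inputs reproduce the 90% but not the 80%

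*Protocol article*

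**What the plan says.** All the relevant statements are in the protocol article, section Sample size calculation.

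- Target effect: "We have powered to detect a standardised effect size of 0.36". For the Beck Scale for Suicide Ideation (BSSI): "This equates to an approximate mean difference of 3.9 in the primary outcome".
- Clustering: seven practitioners in the therapy arm, "average number of patients per practitioner of 18 and ICC = 0.01", with Poisson variation in caseload. The control arm is treated as unclustered.
- Correlation: "We assume a conservative baseline-endpoint correlation of 0.6 (0.6 in pilot, 95% CI 0.4–0.7").
- Error rates: "a two-sided significance level of 0.05 and statistical power of 90% with equal allocation to two arms".
- Conclusion, in the next sentence: "Given these assumptions, an analysis set of 250 (125 per group) has 80% power to detect an effect size of 0.36". It opens by referring back to the assumptions just listed.
- A further sentence says that baseline covariates will raise power where possible.

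The 250 is then inflated to 360 recruited for attrition of up to 30%.

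**The concern.** Two consecutive sentences attach different power to one design. Both cannot hold for the same inputs, and the text does not say that they describe different analyses.

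The figure matters because BSSI is the first-ranked primary outcome. The section Data analyses of the RCT bars any confirmatory claim on suicidal behaviour until benefit has been shown on BSSI, so the power of the BSSI comparison governs both co-primary outcomes. If the trial finds no difference, a reader will want to know whether its chance of missing the target effect was about 10% or about 20%. The section gives both answers.

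Two smaller points affect how the figure is read. The text does not say whether 0.36 is standardised by the raw SD or by the SD left after baseline adjustment. It also calls the correlation of 0.6 conservative while reporting 0.6 as the pilot estimate.

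**Working it through.** **Inputs** (all from Sample size calculation): d = 0.36; r = 0.6; ICC = 0.01 in the therapy arm and 0 in control; mean caseload 18; 7 practitioners; two-sided α = 0.05; 125 per group.

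**Formulas.** With the outcome scaled to a raw SD of 1:

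- Design effect, therapy arm: DE = 1 + 17 × 0.01 = 1.17 for equal caseloads, or 1 + 18 × 0.01 = 1.18 for Poisson caseloads.
- Variance of the adjusted difference: V = V₁ + V₀, where V₁ = (1 − r²) × DE/125 and V₀ = (1 − r²)/125.
- Normal approximation: power = Φ(d/√V − 1.96).
- The same quantity was also taken from a noncentral t, once with 248 df and once with Satterthwaite df, df = V² / (V₁²/6 + V₀²/124). The latter allows for only 7 practitioners (6 df) in the therapy arm.

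**All listed inputs, Poisson caseloads.**

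- 1 − r² = 0.64, so V₁ = 0.64 × 1.18/125 = 0.00604 and V₀ = 0.64/125 = 0.00512.
- V = 0.01116 and √V = 0.1057.
- d/√V = 0.36/0.1057 = 3.41.
- Normal: Φ(3.41 − 1.96) = Φ(1.45) = 0.926.
- t with 248 df: 0.924.
- Satterthwaite df = 19.8: 0.899.

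Equal caseloads (DE = 1.17) give 0.927, 0.925 and 0.901. So 90% is reproduced, closely with practitioner-level df and with 2 to 3 points to spare under the large-sample formulas.

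**Looking for the 80%.** The same calculation with one input changed at a time, or two where shown:

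| r | ICC | Normal | t, 248 df | Satterthwaite t |
|---|---|---|---|---|
| 0.6 | 0.01 | 0.926–0.927 | 0.924–0.925 | 0.899–0.901 |
| 0.6 | 0 | 0.945 | 0.943 | not applicable |
| 0.4 | 0.01 | 0.845–0.846 | 0.842–0.844 | 0.807–0.809 |
| 0 | 0.01 | 0.778–0.780 | 0.775–0.777 | 0.736–0.739 |
| 0 | 0 | 0.812 | 0.809 | not applicable |

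Ranges cover DE = 1.18 and 1.17. If the ICC is taken on the unadjusted variance and r reduces only the variance within practitioners, the result is 0.915–0.917. No version that uses r = 0.6 with ICC 0.01 comes down to 80%. Dropping the correlation does: 81% with no clustering, 74–78% with ICC 0.01. For example, with r = 0 and no clustering, √V = √(2/125) = 0.1265, d/√V = 2.846 and Φ(2.846 − 1.96) = 0.812.

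**Which SD.** 3.9/0.36 = 10.8. If 10.8 is the raw SD, the rows above apply as they stand. If it is already the baseline-adjusted SD, the gain from r = 0.6 has been used up: power is that of the r = 0, ICC 0.01 row (74–78%), and the effect on the raw-SD scale is 0.36 × √0.64 = 0.29.

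**Recruitment.** 250/0.7 = 357.1, so 358 are needed. The planned 360 gives 360 × 0.7 = 252 analysed, which is consistent.

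**The case against.** The strongest defence is that the two figures describe two analyses: 80% for an unadjusted t-test, and 90% once baseline BSSI is in the model. The sentence saying that covariates will raise power points that way, and 81% without correlation or clustering is close to 80%. This is a plausible origin, but the text does not say it. The 80% is tied to the listed assumptions, and those include the correlation of 0.6 and the clustering. The explanation would supply a label for the 80%; it does not make the sentence correct.

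A reader might go further and infer that neither figure follows, since the large-sample formulas give 92–93% rather than 90%. The documents do not support that. The section describes a t-test built for partial nesting with seven practitioners, and practitioner-level df give 0.899–0.901. The exact algorithm of the cited Stata routine was not run, so this does not prove how the sponsor obtained 90%. It is enough to show that 90% cannot be called wrong. For the same reason, putting 92% in its place, or claiming that clearly fewer than 250 analysed would suffice for 90%, would rest on the large-sample formula alone.

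A reader might also want the word conservative struck from the ICC. The section admits that it has no prior estimate and makes the claim relative to psychotherapy trials in general. Whether 0.01 is conservative in that sense depends on literature outside the documents, so the point is not raised. The correlation is different, because the pilot estimate and its interval are printed beside the claim.

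Finally, the error changes neither the design nor the planned analysis, which adjusts for baseline BSSI. That stands, and it keeps the correction to wording.

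**Conclusion.** Wrong as written. One section gives two power figures, 10 percentage points apart, for one design. With the listed inputs and 0.36 read as a raw-SD effect, power at 125 per group is about 90% (practitioner-level df) to 92–93% (large-sample). The 90% stands and the 80% does not follow.

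The result depends on r = 0.6. The pilot interval runs from 0.4 to 0.7, and at 0.4 power is about 81–85%. Since 0.6 is the pilot point estimate, it is not a cautious choice within that interval.

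The sample size is not in doubt under the stated assumptions. If 0.36 was standardised by the baseline-adjusted SD, power would be 74–78%, so the SD needs to be named.

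**What to change.** In Sample size calculation:

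1. Give one power figure: about 90% for an effect of 0.36 with 125 analysed per group, at r = 0.6 and therapy-arm ICC 0.01.
2. Remove the 80%, or keep it with an explicit label as approximate power without baseline adjustment, and say whether it includes clustering (81% without, 74–78% with ICC 0.01).
3. State whether 0.36 is relative to the raw SD (3.9/0.36 = 10.8) or the baseline-adjusted SD. If it is the adjusted SD, the figure in step 1 must be recalculated.
4. Drop the word conservative for the correlation, and report that power is about 81–85% at the pilot lower limit of 0.4.

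With the raw-SD reading the cost is wording only: 250 analysed and 360 recruited stay as they are, and the planned analysis does not change.

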#### Trial Interventions

The trial interventions described below have been specified according to existing policy and procedure [57] and the original treatment protocols [73],Tarrier et al., 2013). The delivery of the PROSPECT programme components will be regularly monitored using audio recordings of therapy sessions.

##### Treatment As Usual (TAU)

Participants randomised to the TAU group will receive the standard care according to national and local service protocols and guidelines. HM Prison and Probation Service (HMPPS) supports prisoners identified to be at risk of suicidal behaviour using a care-planning system called the Assessment, Care in Custody, and Teamwork (ACCT) system. On any one day, over 2000 prisoners in England & Wales are identified under the ACCT system [59]. Typically, individual prisoners receive a risk assessment when a potential risk to self is first identified by staff, which then informs a risk management plan of how to keep the individual safe (e.g. levels of monitoring and observation). Additionally, a referral may be made to the prison’s Mental Health Team that can offer psychosocial assessments, pharmacological therapies and nursing support. Treatment as usual will also include routine care provided by the prison’s general practitioner. The prison GP will be informed that the participant is taking part in the trial and the nature of the study.

